### Demographic variables

Demographic variables included age, gender, nationality, country of birth (of participants and their parents), residence permit status, religion, marital status, household composition and educational level. Participants leaving women’s shelter facilities who were married or divorced were asked if their marriage had been arranged (for example, by family members).

### Secondary outcome measures

The following secondary outcomes were measured in both studies:

• Care needs were assessed using an instrument developed for these studies. For seven domains, participants were asked to indicate whether they wanted help, whether they received help in this area, and whether this was the right help. The domains, which have been subdivided into several items, are housing & daily life (finding housing, maintaining housing, household care, self-care), finances & daily activities (finances, daily activities and recreation, finding work, literacy, transport/mobility), physical health (physical health, alcohol abuse, drug abuse, dental care, nourishment), mental health (mental health, empowerment), safety & protection against violence (protection of own safety, protection of others against own behaviour), social relations (relationship with family, social contacts with friends or acquaintances, relationship with partner), and children (help with contact with children, help for children). Response categories were adopted from the short form Quality of Life and Care (QoLC) [63].

• Self-esteem was evaluated using the Dutch version of the 10-item Rosenberg Self-Esteem scale (RSES) [64,65]. Answers could be given on a four-point scale ranging from *strongly agree* to *strongly disagree*. The RSES shows satisfactory reliability and validity with samples of abused women, with alphas generally between .80 and .90 [66,67]. This instrument has also been used in several studies among homeless people and shows high internal consistency [68].

• The De Jong Gierveld & Kamphuis Loneliness Scale [69] was used to measure loneliness. The scale consists of five positive and six negative items, which are answered with *yes*, *more or less* or *no*. One of the positive items is ‘There are many people I can trust completely’ and a negative item is ‘I miss having people around me’. This scale has been applied in several studies among a range of populations and shows sufficient reliability and validity [70].

• Social support was measured by five items used in the RAND Course of Homelessness Study [71], which were derived from scales developed for the Medical Outcome Study (MOS) Social Support Survey [72]. Participants were asked to indicate how often different kinds of support were available to them through family, friends or other acquaintances, and a partner (if applicable). For each potential source of support, they were asked how often this source was available to (1) have a good time with, (2) provide them with food or a place to stay, (3) listen to them when they were talking about themselves or their problems, (4) accompany them to an appointment to provide moral support, and (5) show that he or she loves and cares for them. A five-point scale ranging from *none of the time* to *all of the time* was used to score the perceived support. The MOS Social Support Survey has been used in several studies among homeless people [73,74]. The 19-item survey showed high convergent and discriminant validity and internal consistency reliability coefficients range from .91 to .97 for the four subscales [72].

• The frequency and intensity of substance use was measured with items from the Dutch translation of the European version of the Addiction Severity Index (EuropASI) [75,76]. The Addiction Severity Index has frequently been used in surveys among homeless people with serious mental and/or addiction problems [77,78]. Studies among substance-abusing populations show satisfactory results for the reliability and validity of the EuropASI [79].

• The Dutch version of the Brief Symptom Inventory (BSI-53) [80,81] was used to assess psychological distress. The BSI consists of 53 items covering nine symptom dimensions: somatisation, obsession-compulsion, interpersonal sensitivity, depression, anxiety, hostility, phobic anxiety, paranoid ideation and psychoticism. Items are measured on a five-point Likert scale, ranging from *not at all* to *extremely*. The BSI has widely been used in research among homeless people and abused women to measure mental health [82,83]. The Dutch version of the BSI demonstrates good reliability and validity [81].

• Service use was evaluated with a self-constructed questionnaire used in several studies by the Netherlands Centre for Social Care Research. Participants were asked to indicate whether they had used the services of certain care providers (e.g. general practitioner, dentist and social services) in the past nine months and in the past 30 days.

• To assess the working alliance between participants and professionals the short version of the 36-item Working Alliance Inventory (WAI) [84-86] (Flemish translation) was used. We simplified the description of items to make them comprehensible for our target groups. The WAI is commonly used in psychotherapy to assess therapeutic alliance and has been extensively studied in this context [87]. Participants assessed the working alliance with their CTI worker or case manager on a seven-point Likert scale ranging from *never* to *always*. The validity and reliability of the English version of the 36-item WAI has been demonstrated to be good [88].

• Experiences with shelter and community care services are evaluated with the Consumer Quality Index for Shelter and Community Care Services (CQI-SCCS) [89]. The CQI-SCCS consists of four scales: ‘Living Conditions’ (six items), ‘Client-Worker Relationship’ (four items), ‘Services Received’ (10 items), and ‘Results of Services’ (five items). The items are scored on a four-point scale ranging from *never* to *always*. Construct validity of the CQI-SCCS is good and test-retest reliability sufficient [89].

In the women’s shelter study the following secondary outcomes are also measured:

• Re-abuse was measured with one single question: ‘Have you been abused since the last interview?’ Answers were *yes* or *no*. Participants were also asked what kind of violence they experienced: 1) ‘physical violence, like being beaten, or he or she threw objects at you’, 2) ‘sexual violence, like intimacy you didn’t want or like’ and 3) ‘emotional violence like threats, or he or she had no respect for your feelings, or said things to hurt you’. Answers were *yes*, *no* or *no information*.

• Symptoms of depression in the week prior to the interview were measured using the Dutch version of the Centre for Epidemiological Studies Depression scale (CES-D) [90,91], a well-established measure of depressive symptomatology. This instrument has been used in several studies among abused women [92,93]. The CES-D contains 20 items rated on a four-point scale ranging from *seldom or never* to *always or almost always*. The CES-D demonstrates good internal reliability, with coefficients ranging from .87 to .93 in research among a general population [90]. Additionally, CES-D demonstrates convergent validity, because it correlates with other measures of depression, as well as sound construct validity [90]. The Dutch version of the CES-D demonstrates acceptable psychometric qualities [91].

• Post-traumatic stress symptoms were measured using the Dutch version of the Impact of Event Scale (IES) [94,95]. The IES is a self-report instrument used in studies among abused women [25,96] and measures changes in reaction to potentially traumatic events. It consists of 15 items, seven of which are related to intrusion (e.g. thinking about the event despite not wanting to do so or having dreams about it) and eight are related to avoidance (e.g. staying away from reminders of it or not wanting to talk about it). The items of the Dutch version of the IES are scored on a four-point scale: *not at all*, *seldom*, *sometimes* and *often*. The Dutch IES has adequate internal consistency with reliability coefficients varying from .87 to .96 for the total score [97].

• Parenting Stress was assessed using two scales of the experimental version of the Parenting Stress Index [98]: ‘Problems with parent–child relationship’ and ‘Problems with parenting’. These two scales contain 22 items rated on a four-point scale ranging from *not true* to *very true*. Two of the items are ‘When I am with my child I feel good’ and ‘I know I am doing a good job as a parent’. The instrument demonstrates good construct validity and good reliability [98].

### Sample sizes

The required sample size for the women’s shelter study is based on the amount of improvement in the subjective quality of life score resulting from the intervention. No information is available from earlier experimental research about what amount of improvement is to be expected. In a study of advocacy services for women leaving shelters, a small but statistically significant difference was found on a similar subjective quality of life scale. At the 12-month follow-up, an effect size of .2 was found: women in the experimental group reported a mean score of 5.08 (SD=1.01) while controls reported 4.87 (SD=1.04) [39]. Since the duration and intensity of the intervention tested in the current trial are much greater than those of the advocacy intervention, a much larger improvement in the subjective quality of life score is to be expected. To calculate the required sample size, we assumed a clinically relevant effect size of .55, resulting in a mean improvement in the subjective quality of life score of .8 (SD=1.5). To detect this difference with 80% power (α = .05, two-sided), each group should contain 55 participants. We considered a potential loss of power due to clustering of data in case managers. Assuming an intra-class correlation coefficient (ICC) of .05 and an average number of three clients per case manager, the number of participants in the experimental and control group should both be increased to 61. Accounting for 30% attrition, the intended sample size is 174 for the total group.

Regarding the homeless shelter study, the sample size calculation is based on the difference between groups in the proportion of participants who become homeless. The expected mean difference is based on a study conducted by Susser et al. [10], who compared clients with severe mental illness receiving CTI in addition to care-as-usual when transitioning to community living to controls receiving care-as-usual only. In the last month of the 18-month follow-up 8% of the group receiving CTI was homeless compared to 23% of the controls. Each group should contain 91 participants to detect this difference with 80% power (α = .05, two-sided) in the current study. Assuming the ICC to be .05 due to clustering of clients in case managers and an average number of five clients per case manager, the number of participants in each group should be increased to 109. Accounting for 30% attrition, the intended sample size is 312 for the total group.

### Analyses

Statistical analyses will be performed using the software program IBM SPSS Statistics for Windows, Version 20.0. Differences in baseline characteristics (e.g. age, gender, education, nationality) between the intervention and control groups will be checked. The primary outcomes of the studies (improvement of quality of life during the nine-month follow-up and decrease in days unhoused over nine months), as well as other outcomes, will be compared between groups according to the intention-to-treat principle using mixed-effects analyses to correct for clustering. Quality of life at baseline will be added as covariate. Dichotomous outcomes will be compared using multi-level logistic regression and odds ratios will be reported. In the analyses corrections will be made for important characteristics such as age, gender, duration of victimisation, duration of homelessness and severity of psychological problems.

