### Selection of recruitment settings and clients

Shelter facilities were eligible for selection as recruitment settings if their organisation was participating in the Academic Collaborative Centre for Shelters and Public Mental Health in 2009. Furthermore, shelter facilities needed to provide 24-hour services, serve at least 50 different clients aged 18 or older per year, and expect to continue their services over the next five years. They also had to provide services to clients who usually spend no longer than 12 months in the shelter facility. An additional criterion for shelter facilities for abused women was that they needed to provide care to clients who usually spend at least six weeks in the shelter. Shelter facilities were not included in the selection if their services were limited to a specific group of clients, such as drug users or teenage mothers, or if they already offered care which was very similar to CTI.

Out of the shelters matching these criteria and willing to participate, we selected at least one and at most four facilities per organisation and ensured selected shelter facilities were distributed evenly among the four regions of the Netherlands (north, east, south and west). Nineteen women’s shelters (run by nine organisations) and 22 shelters for homeless people (run by nine organisations) participated in the studies. These shelter facilities for homeless people could be best characterised as transitional housing facilities. Some participants recruited in these facilities have not experienced literal homelessness, seeing that not all of them have spent time on the street, in emergency shelters or doubled-up with family or friends before entering these facilities. However, the participants may be characterised as homeless persons using a broader definition; all participants entered these transitional housing facilities because they lacked the resources or support networks needed to obtain housing [53].

Clients were eligible for participation if they:

• were aged 18 years or older;

• were willing to receive support from the shelter organisation during and after leaving the shelter facility;

• were staying in the shelter facility due to intimate partner or honour-related violence (abused women);

• had been staying in the shelter facility for at least six weeks (abused women);

• would be staying in the shelter facility for no longer than 14 months at the date of departure (homeless people);

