### Randomisation and blinding

Randomisation was stratified according to shelter location. Before the start of these studies two allocation schedules were generated using the Random Integer Set Generator at http://www.random.org/integer-sets, which employs a restricted randomisation procedure. The random numbers were secured in a digital file and concealed until conditions were assigned. To avoid periodic imbalance, block randomisation was used: out of every four participants, two were randomly assigned to the experimental group. One of two researchers allocated the participants after the first interview and depending on the condition to which a client was allocated, a CTI worker or case manager initiated the assigned care.

Shelter staff, including the contact person who screened clients for eligibility, did not have any foreknowledge of condition assignment; they were informed about the assigned condition after the first interview had been conducted. Clients agreed to participate in the study before randomisation and without knowing in which condition they would be enrolled. They were blinded to allocation until they met their CTI worker or case manager after the first interview. The researchers withheld information about allocation from the research assistants, who conducted the interviews with participants, to ensure that these assistants were blinded from condition assignment.

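### Shelter location, the only stratification factor, is not named in the analysis model and the clustering level is undefined; if shelter is omitted, standard errors will tend to be too wide

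*Protocol article*

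**What the plan says.** Under Randomisation and blinding the article states: "Randomisation was stratified according to shelter location". Allocation was blocked: "out of every four participants, two were randomly assigned to the experimental group". No other stratification factor is given. The strata are numerous: "Nineteen women’s shelters (run by nine organisations) and 22 shelters for homeless people (run by nine organisations) participated in the studies" (Selection of recruitment settings and clients).

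The Analyses section compares groups "according to the intention-to-treat principle using mixed-effects analyses to correct for clustering", and uses multi-level logistic regression for dichotomous outcomes. It adds covariates: "Quality of life at baseline will be added as covariate", and "corrections will be made for important characteristics such as age, gender, duration of victimisation, duration of homelessness and severity of psychological problems". Shelter location is not mentioned there as a fixed effect, random effect or covariate, and no level of clustering is defined.

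The unit of clustering is named only under Sample sizes: "We considered a potential loss of power due to clustering of data in case managers". That text assumes an intraclass correlation (ICC) of .05 with three clients per case manager in the women's study and five in the homeless study. The control-condition section says that CTI workers gave no services to control participants. The CTI section says that case managers were assigned for CTI training by organisation, at least two each.

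**The concern.** Blocking within shelter gives each shelter roughly equal numbers in both arms, so differences between shelters largely cancel from the treatment contrast. The analysis recovers that gain only if it knows about the shelters. A case-manager random effect does not do this. CTI workers and control case managers are different people, so each case manager belongs to one arm, and a shelter effect shared by both arms looks to such a model like extra variance between case managers, or like residual variance. Either way it is added to the standard error of a contrast from which the design has removed it.

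At stake is precision. Confidence intervals would be wider and p-values larger than the randomisation warrants. The women's study plans on an effect size of .55, while the one earlier study that the article cites found .2, so there is little room to lose power.

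**Working it through.** **The plan's own figures.**
- Women: 2 × (1.960 + 0.842)² × (1.5/0.8)² = 55.2 per group; a standard calculation rounds up to 56, the article states 55. Design effect 1 + (3 − 1) × 0.05 = 1.10; 55 × 1.10 = 60.5, so 61. Total 2 × 61/0.7 = 174.3, stated as 174.
- Homeless: 8% versus 23% gives 91 per group. Design effect 1 + (5 − 1) × 0.05 = 1.20; 91 × 1.20 = 109.2, stated as 109. Total 2 × 109/0.7 = 311.4, so 312.

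These figures reproduce to within rounding and are not at issue. They show that the planned inflation covers case managers only.

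**Inputs for the check.** Case-manager ICC rc = 0.05 and clients per case manager m = 3 (women) or 5 (homeless), both from Sample sizes. The shelter share of variance, rs, is not in the article; 0 to 0.10 is assumed.

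**Formulas.** Take total variance as 1. The variance of the treatment difference is proportional to:
- shelter in the model (correct): C = (1 − rs − rc) + m·rc
- shelter omitted, its variance absorbed at case-manager level: A = (1 − rs − rc) + m·(rc + rs)
- shelter omitted, its variance absorbed in the residual: B = (1 − rc) + m·rc

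The standard error is inflated by √(A/C) or √(B/C).

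**Worked at rs = 0.05.**
- Women: C = 0.90 + 0.15 = 1.05; A = 0.90 + 0.30 = 1.20; B = 0.95 + 0.15 = 1.10. √(1.20/1.05) = 1.07; √(1.10/1.05) = 1.02.
- Homeless: C = 0.90 + 0.25 = 1.15; A = 0.90 + 0.50 = 1.40; B = 0.95 + 0.25 = 1.20. √(1.40/1.15) = 1.10; √(1.20/1.15) = 1.02.

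| Assumed shelter ICC | Women: residual / case-manager level | Homeless: residual / case-manager level |
|---|---|---|
| 0 | 1.00 / 1.00 | 1.00 / 1.00 |
| 0.02 | 1.01 / 1.03 | 1.01 / 1.04 |
| 0.05 | 1.02 / 1.07 | 1.02 / 1.10 |
| 0.10 | 1.05 / 1.14 | 1.04 / 1.21 |

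**Consequence for the test.** With inflation r, the two-sided error rate is 2 × [1 − Φ(1.96r)], and a nominal 80% power becomes Φ(2.80 − 1.96r). At rs = 0.05 with case-manager absorption, the error rate is 0.036 (women) and 0.031 (homeless), and power is 76% and 74%. With residual absorption the error rate is about 0.045 in both and power about 79%.

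**Simulation of the case-manager version.** 40,000 balanced trials per setting, continuous outcome, one case manager per arm per shelter (19 × 2 × 3 and 22 × 2 × 5). An unpaired t-test on case-manager means stood for omitting shelter, a paired t-test within shelter for including it. Under no effect at rs = 0.05:
- Women: standard error 0.2055 without shelter and 0.1923 with it, against an empirical SD of 0.191; rejection rate 0.037 and 0.049.
- Homeless: 0.1596 and 0.1446, against 0.145; rejection rate 0.032 and 0.051.

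Under an effect (0.55 women, 0.4 homeless), power without and with shelter was:

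| Assumed shelter ICC | Women | Homeless |
|---|---|---|
| 0 | 0.779 / 0.756 | 0.755 / 0.736 |
| 0.02 | 0.770 / 0.763 | 0.736 / 0.742 |
| 0.05 | 0.755 / 0.775 | 0.704 / 0.750 |
| 0.10 | 0.731 / 0.792 | 0.656 / 0.768 |

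The paired test spends degrees of freedom, so in this comparison the net power gain is about nil, or slightly negative, at 0 to 0.02. It becomes material at 0.05 and above. The logistic models were not simulated.

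**The case against.** The strongest case on the other side is that nothing in the article says shelter is excluded. A reader might infer that it has been left out, or that the analysis corrects for clustering and nothing else. The text supports neither inference. The Analyses section also adjusts for baseline quality of life and for several characteristics, its covariate list is open-ended, and its clustering levels are unnamed and could include shelter. The case manager is the named unit only in the sample-size reasoning, and a design-effect assumption does not define the analysis model. The article is a condensed account, and an analysis plan that is not shown may settle the matter.

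The size is also uncertain. The larger figures put all shelter variance at case-manager level, with one worker per arm per shelter. Workers were assigned by organisation and may have served several shelters. Usual care varied widely and could include referral elsewhere. Residual absorption gives only about 2% at an ICC of 0.05. Covariates would take up some of the shelter variance, and if shelters do not differ there is no inflation.

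All of this stands, and it limits the point to what is not named and what follows if shelter is omitted. It does not remove the point. The article describes a model and lists its covariates, yet does not mention the one factor built into the allocation. If clustering there means shelter, then the case-manager clustering that raised the group sizes from 55 to 61 and from 91 to 109 is the level left unnamed. On either reading the levels need stating.

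**Conclusion.** The point holds as a conditional one of minor to moderate weight. The stratification factor is not named in the analysis model and the clustering level is undefined. If the model carries only case-manager clustering and the listed covariates, standard errors will tend to be too wide: nil at a shelter ICC of 0, about 2% to 7-10% at 0.05, and about 4-5% to 14-21% at 0.10. At 0.05 that is a loss of precision equal to 4-5% of the sample if the variance goes to the residual (1 − 1.05/1.10 and 1 − 1.15/1.20). It is 12.5% (women) to 18% (homeless) if it goes to case-manager level (1 − 1.05/1.20 and 1 − 1.15/1.40).

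These figures rest on an assumed shelter ICC, balanced data, a continuous outcome and no help from covariates. A reader might go further and call the reported standard errors wrong, or the trial at risk of a false-positive result. The first depends on a model that the article does not fully specify. The second runs against the direction of the error, which is conservative. The calculation shows no bias in the effect estimate, and the stated sample sizes are unaffected.

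**What to change.** State in the Analyses section that shelter location enters every primary and secondary outcome model as a random effect, with case manager as a further random effect. Do not assume that each case manager sits within a single shelter, since workers were assigned by organisation. For a logistic model that does not converge, pre-specify organisation or region in place of shelter.

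Avoid fixed shelter effects in the logistic models. The planned completers come to about 6 per women's shelter (122/19) and 10 per homeless shelter (218/22). At the planning rates of 8% and 23%, the homeless study would have about 109 × 0.08 + 109 × 0.23 = 34 events over 22 shelters, or 1.5 per shelter.

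The cost is a sentence in the plan and one term per model. Shelter is already recorded for randomisation. If shelters turn out not to differ, the price is at most a small loss of degrees of freedom.

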### Baseline and follow-up measurements and retention rates

Outcome measurements took place before participants left the shelter facility and at three, six and nine months after shelter exit (see Figure 1). Ideally, the first interview was planned up to four weeks before leaving the shelter facility, because the preparatory phase of CTI should be initiated before the transition. If this was not possible, the interview took place up to two weeks after shelter exit. The second and third interviews were held by phone.

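### Quality of life is the only outcome baseline named as a covariate, so the other continuous scales are not stated to be adjusted for their own baseline

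*Protocol article*

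**What the plan says.** The Analyses section of the protocol article first names the two primary outcomes, then extends the same method to the rest: "as well as other outcomes, will be compared between groups according to the intention-to-treat principle using mixed-effects analyses to correct for clustering". The next sentence is "Quality of life at baseline will be added as covariate". It names no outcome to which it is limited. The section ends with an open list: "corrections will be made for important characteristics such as age, gender, duration of victimisation, duration of homelessness and severity of psychological problems".

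The section on baseline and follow-up measurements states "Outcome measurements took place before participants left the shelter facility and at three, six and nine months after shelter exit", and allows the first interview up to two weeks after exit where an earlier one was not possible. Under Randomisation and blinding, allocation follows the first interview, so values from that interview precede randomisation.

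The continuous secondary scales include self-esteem ("Self-esteem was evaluated using the Dutch version of the 10-item Rosenberg Self-Esteem scale (RSES"), loneliness (the scale that "was used to measure loneliness"), social support and the BSI (which "was used to assess psychological distress"). The women's study adds the CES-D, the IES and parenting stress. Quality of life is primary for the women and secondary for the homeless participants.

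**The concern.** The covariate sentence can be read in two ways, and neither serves the secondary scales well.

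- **It applies to every model.** This is the literal reading, because the preceding sentence covers all outcomes. Baseline quality of life is then the named baseline for self-esteem, loneliness, social support, depression, trauma symptoms and parenting stress. For each of these it is the baseline of a different variable.
- **It applies to the quality-of-life outcome only.** The term is then correct there, but nothing is stated about an own-baseline term for the other scales.

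An outcome's own baseline is usually its strongest available predictor. Leaving it out gives up precision and leaves any chance baseline difference on that scale uncorrected. Both trials are of moderate size (61 and 109 evaluable participants per arm planned), so the loss could matter for secondary outcomes. An unclear rule also leaves the choice of covariates open across many outcomes.

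**Working it through.** **1. The plan's own sample sizes (Sample sizes section).** These fix the numbers per arm used below.

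- Women: 2 × [(1.960 + 0.842) × 1.5 / 0.8]² = 55.2 per arm; the plan states 55. The design effect is 1 + (3 − 1) × 0.05 = 1.10, and 55 × 1.10 = 60.5, stated as 61. Attrition: 122 / 0.7 = 174.3, stated as 174.
- Homeless: 8% against 23% gives 91 per arm, as stated. The design effect is 1 + (5 − 1) × 0.05 = 1.20, and 91 × 1.20 = 109.2, stated as 109. Attrition: 109 / 0.7 = 155.7, so 156 per arm and 312 in total, as stated.

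The figures reproduce. None of them uses a baseline covariate, so none changes here. Effective numbers per arm after clustering are 61 / 1.10 ≈ 55 and 109 / 1.20 ≈ 91.

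**2. Own baseline against no baseline adjustment.** Let r be the correlation between baseline and follow-up on the same scale. The documents give no value for any scale, so r = 0.3, 0.5 and 0.7 are assumptions.

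- Residual variance factor: 1 − r².
- Detectable difference in SD units at 80% power, two-sided 5%: (1.960 + 0.842) × √(1 − r²) × √(2/n).

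| r | Variance factor | Standard error smaller by | Detectable, n = 55 | Detectable, n = 91 |
|---|---|---|---|---|
| 0 | 1.00 | – | 0.53 | 0.42 |
| 0.3 | 0.91 | 5% | 0.51 | 0.40 |
| 0.5 | 0.75 | 13% | 0.46 | 0.36 |
| 0.7 | 0.51 | 29% | 0.38 | 0.30 |

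**3. Own baseline against baseline quality of life only (the literal reading).** Let q be the correlation of baseline quality of life with the follow-up scale, assumed to be 0.2 to 0.4. The variance ratio is (1 − r²) / (1 − q²).

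- Smallest gain, r = 0.5 and q = 0.4: 0.75 / 0.84 = 0.893, so 11% lower variance.
- Largest gain, r = 0.7 and q = 0.2: 0.51 / 0.96 = 0.531, so 47% lower variance.
- For an assumed true difference of 0.3 SD and n = 55 per arm, power is 0.36 to 0.40 with quality of life only and 0.44 to 0.60 with the own baseline (r = 0.5 to 0.7).

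**4. Own baseline against a change-score analysis.** A change score has variance factor 2(1 − r). At r = 0.7 that is 0.60, and 0.51 / 0.60 = 0.85, so the gain is 15%.

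**5. What the listed covariates cover.** Severity of psychological problems could stand for baseline BSI, and would probably relate to the CES-D and IES as well, but no instrument or time point is given. Nothing on the list is an own baseline for self-esteem, loneliness, social support or parenting stress.

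**The case against.** The strongest reply is that this turns silence into a fault. The text excludes no own-baseline term, the covariate list is open, and covariates for each secondary outcome are ordinary content of a full protocol or analysis plan that is not shown. That stands against any claim that these scales *will not* be adjusted for their baseline; a reader might infer this, but the article does not say it. It does not dispose of the point. The article goes beyond silence by stating a baseline covariate within a description that covers all outcomes, and the one it states suits only the quality-of-life outcome.

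Three further replies have force.

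- Distress is a weak example, for the reason given in step 5.
- A mixed model that takes the baseline interview as a repeated response would use each scale's own baseline without a covariate. The article does not say which form is meant, so this remains possible.
- The largest gains assume high correlations and a wholly unadjusted comparator. At r = 0.3 the detectable difference barely moves, and against quality-of-life or change-score adjustment the gain shrinks.

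A reader might also infer that days unhoused in the homeless trial lacks a suitable history covariate. It does not: duration of homelessness is already listed, and no harm from also keeping baseline quality of life can be shown from the document.

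**Conclusion.** The point holds as a minor one about a stated rule. Followed literally, the covariate sentence gives most continuous secondary scales another variable's baseline and does not state adjustment for their own.

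It would be wrong to read this as bias: randomisation protects the comparison with or without the baseline term. The cost is possible loss of precision and uncorrected chance imbalance, in secondary outcomes only. Own-baseline adjustment lowers variance by 9% to 49% against no baseline adjustment (r = 0.3 to 0.7), or by 11% to 47% against quality of life alone (r = 0.5 to 0.7, q = 0.2 to 0.4). All these correlations are assumed. Gains are smaller still where other listed covariates already explain variance. The figures also assume that each scale was part of the first interview. The measurement section says this of outcomes in general but gives no schedule by instrument in the text available. The women's primary analysis and both sample sizes are unaffected.

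**What to change.** Replace the covariate sentence with: *Each continuous outcome measured at baseline is adjusted for its own baseline value (quality of life at baseline for the quality-of-life outcome).* If the baseline interview is instead meant to enter the mixed model as a repeated measure, say so there. No change is needed for days unhoused.

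The cost is one sentence, settled before analysis. The baseline data come from an interview already in the design, and no planned number changes.
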